#### Sample size

We expect that HRV will decrease in both groups at T1 compared with T0, with a smaller decrease in the EMD group, resulting in greater HRV at T1 in the EMD group compared with the EMD retrieval-only control group. No studies have been carried out yet comparing the effect of EMD to retrieval only on HRV in PTSD patients to inform power calculations. However, based on the theoretical assumptions and studies with other related outcome measures [63, 64], we expect to detect a difference between the EMD condition and retrieval only on HRV of a medium effect size (Cohen’s *d* = 0.4). Power calculations were conducted using G*power software and were based on based on a general linear model (GLM). Linear mixed-effect model can be conceptualized as GLM (repeated measure ANOVA) as a balanced design within independent sampling units, and an unstructured covariance model is assumed [65]. We transformed for Cohen’s *d* = 0.4 into *f* = 0.2. For a 2 between (treatment EMD conditions) X 2 within (baseline, post-treatment) repeated measure ANOVA (*α* = 0.05, power = 0.9, correlation between measures = 0.4, and medium effect-size *f* = 0.2) [7, 66]. A power calculation suggested that a total sample size of *N* = 82 will be required, which is 41 per condition. All power computations were conducted in the G*Power software. Considering drop out of participants, we will recruit an additional 25% extra participants, yielding a total number of 55 participants per condition, thus 110 participants in total.

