#### Statistical analysis

Baseline sociodemographic and outcomes of interest are first compared across treatment conditions. Data will be described by reporting results from general descriptive analysis. The categorical variables will be summarized as numbers and percentages and continuous variables as means and standard deviations, minimum, and maximum.

Following this, intention-to-treat analysis will be performed only for the primary outcome, and then performing multiple imputation with a sensitivity analysis using both observed and imputed data. *P* values of < 0.05 will be considered significant.

Statistical analysis will be conducted using R Statistics software. The stress reactivity outcome variables were measured only at T0 and T1. HRV is a primary outcome that is a continuous dependent variable. We will analyze our data using repeated measures analysis of variance (ANOVA) to examine the interaction between time (pre-post intervention), within-subject factor, and the between-group factor treatment group. This analysis allows us to compare the two groups over time to examine whether participants in the EMD condition benefit more in terms of stress reduction, when compared to the retrieval-only condition, from baseline to post-treatment.

We will analyze the secondary outcomes (self-report and neurocognitive measures) using linear mixed models, with a random effect for participants. Data from time points T0, T1, T2, and T3 will be included in the repeated measures models. In all analyses, a treatment × time interaction term will represent the effect of EMD and EMD retrieval-only interventions of the outcome variables over time. Trauma type, gender, and age will be included as covariates in all models, both for the primary as well as the secondary outcome(s).

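### The primary group-by-time ANOVA is a change-score test: valid and correctly sized at the plan's own inputs, but about 30% less efficient than ANCOVA on T0 HRV at the plan's own correlation of 0.4

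*Protocol article*

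**What the plan says.** The Statistical analysis section of the protocol article fixes the primary model: "We will analyze our data using repeated measures analysis of variance (ANOVA) to examine the interaction between time (pre-post intervention". The same section limits the data to two visits: "The stress reactivity outcome variables were measured only at T0 and T1". It names the term that carries the treatment effect: "In all analyses, a treatment × time interaction term will represent the effect of EMD and EMD retrieval-only interventions". On adjustment it states: "Trauma type, gender, and age will be included as covariates in all models". T0 HRV is not among the listed covariates, and the section does not say whether the covariates interact with time.

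The Sample size section sizes the trial for the same 2 x 2 repeated-measures ANOVA, with f = 0.2 (converted from d = 0.4), alpha 0.05, power 0.9 and "correlation between measures = 0.4". The result is 82 participants (41 per arm), raised to 110 (55 per arm) for dropout.

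The Screening section treats the physiological recording as the second part of the baseline assessment. The Randomization section places randomization after all baseline assessments. T0 HRV is therefore a pre-randomization measurement.

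**The concern.** A change score subtracts the whole baseline value, whatever the correlation between visits. When that correlation is well below 1, the subtraction adds noise. Below 0.5, with equal SDs, the change score is less precise than ignoring the baseline altogether, and the plan's own 0.4 lies in that range. ANCOVA instead weights the baseline by its estimated slope, and it also removes the dependence on chance baseline imbalance in HRV.

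The covariate sentence adds a second issue. Trauma type, gender and age are constant within a person. If they enter the planned ANOVA only as main effects, and every participant has both visits, they explain differences between people and leave the tested within-person interaction as it was. A reader would take the primary result to be adjusted when it is not.

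At stake is precision on the primary question, not the validity of the test.

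**Working it through.** **Inputs.** From the Sample size section: f = 0.2, correlation rho = 0.4, alpha 0.05, power 0.9, N = 82, 25% for dropout. Sidedness is not stated; the ANOVA F test corresponds to a two-sided t-test. Equal SDs at T0 and T1 are an assumption, implied by sizing with a single f and a single correlation. Variances below are in units of the HRV variance.

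**Step 1: reproduce the plan's figure.** For the within-between interaction with m = 2 visits, the noncentrality is lambda = N x m x f² / (1 - rho). At N = 82 this is 82 x 2 x 0.04 / 0.6 = 10.93. With 1 and 80 degrees of freedom, power is 0.904; N = 80 gives 0.897. The smallest even N is therefore 82, as stated. Dropout: 82 / 0.75 = 109.3, so 110, also as stated.

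**Step 2: show that it is a change-score test.** In this formula f = 0.2 equals a between-group difference in change of 4 x 0.2 = 0.8 SD. The change score has variance 2(1 - rho) = 1.20. The squared noncentrality of the t-test is 0.8² x 82 / (4 x 1.20) = 10.93, the same as in Step 1. On one simulated data set, both fits gave an estimate of 0.5119 with SE 0.2378.

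**Step 3: compare the analyses at rho = 0.4.**

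| Analysis | Variance | N for 90% power (f = 0.2) | Power, N = 82 | Power, N = 110 |
|---|---|---|---|---|
| Change score (planned) | 2(1 - 0.4) = 1.20 | 82 | 0.904 | 0.967 |
| T1 alone | 1.00 | 68 | 0.947 | 0.986 |
| ANCOVA on T0 | 1 - 0.4² = 0.84 | 58 | 0.974 | 0.995 |

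The relative efficiency of the change score to ANCOVA is 0.84 / 1.20 = (1 + rho)/2 = 0.70. A simulation of 10,000 trials at N = 82 gave a variance ratio of 0.72, because the slope has to be estimated, and power of 0.909 against 0.971.

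**Step 4: vary the correlation.** From (1 + rho)/2, the loss is 40% at rho = 0.2, 30% at 0.4, 25% at 0.5, 20% at 0.6 and 10% at 0.8. If the SDs differ (s0 at T0, s1 at T1), the change-score variance exceeds the ANCOVA variance by (s0 - rho x s1)². The size of the loss then changes but its sign cannot. With equal SDs and rho = 0.4 the excess is 0.6² = 0.36 = 1.20 - 0.84.

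**Step 5: other reading of the effect size.** If d = 0.4 is taken as a 0.4 SD difference in change, then f = 0.4 / 4 = 0.1. Power is then 0.372 for the change score and 0.497 for ANCOVA at N = 82, and 0.475 against 0.621 at N = 110. The N for 90% power is 318 against 224. The relative gain is about the same, but ANCOVA alone does not reach 90%.

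**Step 6: covariates.** In the simulated data of Step 2, adding covariates as main effects with complete pairs left the interaction at 0.5119 (SE 0.2378). With covariate-by-time terms it moved to 0.4792 (SE 0.2342). In a mixed model with about 25% of T1 missing, main-effect covariates moved it slightly, from 0.5879 to 0.5839.

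**The case against.** The strongest defence is that nothing here is an error. The Primary outcome section states the hypothesis as a between-group difference in the change in HRV, the ANOVA tests that, and the sample size was computed for that test and reproduces. At the plan's f = 0.2 the planned power is already 0.90, so the absolute gain is modest. All of this stands, and it makes the point one of efficiency. It does not remove the point: because T0 precedes randomization, ANCOVA targets the same treatment effect with less variance, and the Sample size section itself expects higher T1 HRV in the EMD arm.

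Stronger readings are tempting, and the documents do not carry them:

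- **That the covariates cannot affect the primary test.** This is exact only for main effects with complete (or imputed) pairs. The article does not give their form. The usual multivariate fit of a repeated-measures ANOVA brings in covariate-by-time terms, and then the adjustment is real.
- **That the trial is already underpowered.** At the stated f = 0.2, N = 82 is correct. Low power follows only if f is replaced by 0.1, and how d = 0.4 should be read is a separate question.
- **That the covariance assumptions contradict each other.** The words "an unstructured covariance model is assumed" belong to the sizing of the two-visit primary design. The self-report and neurocognitive outcomes at T0 to T3 are analysed "using linear mixed models, with a random effect for participants", which concerns other models and does not settle their residual covariance. Nor can an inflated type I error be put on the 3-month contrast, since the article gives no correlations among the four visits.

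**Conclusion.** The point holds as an efficiency weakness in a valid analysis that matches its sample size calculation. At the plan's correlation of 0.4 and equal SDs, the planned test loses about 30% of the information relative to ANCOVA on T0 HRV, and it is less precise than comparing T1 alone (1.20 against 1.00). At the plan's f = 0.2 this is power of 0.90 against 0.97 with 41 per arm, or 82 against 58 participants. If d = 0.4 means a 0.4 SD difference in change, it is 0.37 against 0.50 with 41 per arm.

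The 30% depends on an assumed correlation and on equal SDs; the direction depends on neither. The remark on covariates is conditional on main-effect entry with complete pairs. The change should be made, but the planned result would not be biased without it.

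**What to change.** Make the primary analysis a linear model of T1 HRV on treatment, T0 HRV, age, gender and trauma type. Report the adjusted mean difference between arms with its 95% CI as the primary result. Analyse HR and PEP, which are also measured only at T0 and T1, in the same way. In this model the three listed covariates adjust the treatment effect directly, so the covariate sentence means what it appears to mean.

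The cost is a rewording of the Statistical analysis section, one residual degree of freedom for T0 HRV and a slope to be estimated (a variance ratio of 0.72 in simulation instead of 0.70), which is negligible at 82 to 110 participants. No new data are needed. The sample size can stay as it is, and the gain then serves as a margin.

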## Discussion

RCTs have proven that PTSD treatment using EMDR is effective in reducing PTSD symptoms [5, 6]. This study will compare eye movements to retrieval only to understand the role of EMs within EMD with regard to its effect on stress reactivity and neurocognitive functioning in response to trauma scripts in Indonesian patients diagnosed with PTSD. If the EMD intervention is proven effective in terms of stress reactivity reduction, improved neurocognitive functioning and the reduction of PTSD symptoms shortly after the intervention up to 3 months follow-up, it would give us more insight into the underlying mechanisms of EMD as intervention. This would provide empirical evidence that the additional effect of EMs will extend to stress reactivity measures and may further support the contribution of eye movements and similar dual stimulation tasks to the effectiveness of EMDR treatment.

## Trial status

Protocol (ISRCTN55239132) was registered on 19 December 2017 and recruitment started on 21 April 2019. Recruitment will continue until 31 December 2020.

## Data Availability

The datasets used and/or analyzed during the current study are available from the corresponding author on reasonable request.
